### Procedures

Documented approval has been obtained from the REB of the study site. When an eligible infant becomes available, the research nurse will explain the study to the parents, answer questions, determine the mother’s availability to provide KMC, and obtain written informed consent.

A minimum of 3 painful procedure sessions will be video-recorded with each infant, with each session being a minimum of 24-hours apart. For infants less than or equal to 32 weeks, sessions will be recorded as close to recruitment as possible, at 32 weeks, 36 weeks, and prior to discharge. For older infants, the sessions will be spaced as evenly apart as can be estimated. The research nurse will coordinate the timing of the procedure-recording with the staff, call parents to tell them that the procedure is taking place at a given time, and tell them the KMC condition (i.e., skin-to-skin or standard care).

The research nurse will mark phases on the recordings by holding colored cards briefly in front of the video camera. These phases will include baseline 1 at beginning of monitoring, baseline 2 prior to procedure initiation, heel warming or vein site cleansing, painful procedure (i.e., heel lance or venipuncture), application of bandage, and heart rate return to baseline. The research nurse will ensure that monitoring remains intact, and that the camera is focused on the infants face at an angle that makes the infant appear prone in an incubator in order to keep coders naïve [74]. Phases will be matched to the built in timer of the Somte monitor used to record physiologic data.

Depending on the gestational age of the infant, neurodevelopmental assessments using the Neurodevelopmental Assessment of the Preterm Infant will be conducted at 32 weeks, 36 weeks, and/or term equivalence by a trained research assistant who will be kept blind to group assignment.

Mothers will be asked to keep a diary about the amount of time they provide KMC regardless of group assignment. As one study has demonstrated that mothers stress in the NICU decreases with KMC [86], and as there is a plausible relationship between maternal cortisol levels and infant reactivity [87], there is an interest in studying maternal stress levels over time. Therefore, salivary cortisol samples will be collected from the mothers shortly after enrollment of the infant, halfway through the stay, and near NICU discharge. Samples will be collected near morning awakening in order to obtain basal cortisol levels, which are more reflective of trait anxiety as opposed to state anxiety. This data is exploratory, and will be correlated over time with infant pain response, accounting for group assignment. Mothers will also be asked 2–4 questions (depending on randomization) regarding their experience with providing KMC to their infants during hospitalization.

In addition to having mothers answer questions regarding KMC, nursing staff will also be questioned. At the beginning of the study, nurses will be asked to answer informal investigator questions aimed at assessing their attitudes toward KMC as an intervention for painful procedures. The questionnaires will be repeated every 6 months throughout the study. It is anticipated that nurses will have progressively more positive attitude toward KMC as an intervention as the study progresses. While attempts will not be made to sample the same nurses over time, the purpose of the questionnaire is to generate a sense of the units perceptions of KMC, and thereby understand what issues may arise in terms of fidelity to the study protocol.

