#### Implementation

Group assignment will be acquired by the research nurse from the secure website. The REB approved research nurse is the only individual in this study who has access to the secure site after consent is obtained.

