### Allocation concealment mechanism

The pharmacy at the study site will supply the syringes containing the study solution. Of the study syringes, 1/3 will contain sterile water and 2/3 will contain 24% sucrose. The study solutions will be labeled with a code known only by pharmacy and the research nurse. Solutions will be prepared and packaged in an identical matter. Upon knowing infant group assignment, the research nurse will label each syringe with the infants study number and name to ensure added protection. Each participant will be provided syringes at his/her bedside and the research nurse will conduct regular syringe counts to evaluate compliance.

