#### *Combined KMC and sucrose condition*

For combined sucrose and KMC, the infant will be placed in KMC as described for the KMC alone condition, however, will receive 24% oral sucrose solution as per the NICU protocol described above.

Although most painful procedures will not be video-recorded for the study analysis, the expectation is that the staff caring for infants enrolled in the study will follow the study intervention protocol for all painful procedures, and that any deviations from the study protocol will be charted and included in the analyses. Babies in the KMC group will have reminder signs at the bedside prompting the staff to place them in KMC for procedures, and the study syringes of either 24% sucrose solution or sterile water will be available to staff at the bedside throughout the infant’s stay in the NICU. Staff documentation of all painful procedures will be monitored to ensure compliance with the study protocol.

In order to ensure equipoise, staff may deviate from the protocol to give off-study doses of rescue sucrose if the infant has a PIPP score > 6 (considered to indicate pain) at their discretion. The deviations from protocol will be recorded on a procedure record kept at each infant’s bedside. If the mother is unavailable for a painful procedure, the infant will be swaddled and given the study solution. If the infant has a PIPP score > 6, off-study sucrose may be given by the nurse caring for the patient. All off-study sucrose doses will be recorded in the procedure record and the research nurse will confirm the doses given from the medication administration record.

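### A research nurse who knows the arm arranges which routine procedures become primary-outcome sessions, with a minimum number of sessions but no arm-independent rule for choosing them

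*Protocol article*

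**What the plan says.** All places are in the Protocol article.

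- **Number.** Procedures: "A minimum of 3 painful procedure sessions will be video-recorded with each infant", at least a day apart. No maximum or fixed number is given.
- **Timing, infants of 32 weeks or less.** Procedures: "sessions will be recorded as close to recruitment as possible, at 32 weeks, 36 weeks, and prior to discharge". No window is stated, nor which procedure near each point is taken.
- **Timing, older infants.** Procedures: "For older infants, the sessions will be spaced as evenly apart as can be estimated". No time points and no pre-discharge session are named.
- **Who arranges it.** Procedures: "The research nurse will coordinate the timing of the procedure-recording with the staff".
- **What that person knows.** Implementation: "Group assignment will be acquired by the research nurse from the secure website". Allocation concealment mechanism: "The study solutions will be labeled with a code known only by pharmacy and the research nurse".
- **What the sessions are drawn from.** Combined KMC and sucrose condition: "most painful procedures will not be video-recorded for the study analysis". When the mother is absent the infant is swaddled and given the study solution. Whether such a procedure may serve as a filmed session is not said.
- **What the analysis needs.** Statistical analysis sets time zero at the last period, compares arms there, and tolerates missing data provided three points exist.
- **Protection offered.** Trial design keeps the coders blind. Statistical analysis accepts unequal spacing.

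**The concern.** Blinded coding protects the scoring of a film. It does not protect the choice of what is filmed. That choice is made repeatedly after randomisation, with the arm known, and the article gives no rule that would make it the same in all three arms.

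No bad intent is needed for the arms to drift apart. A KMC session requires the mother to be present, so the practical occasions for filming differ by arm. The background section on Kangaroo Mother Care links quiet sleep to a lower pain response, so the time of day and circumstances chosen can matter for the score. Procedures also anticipates that unit nurses, with whom timing is arranged, will grow more favourable to KMC as the study proceeds.

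Two things are at stake. One is the contrast in mean PIPP, if the filmed occasions are easier in one arm. The other is the contrast at the final assessment, which carries the claim of sustained efficacy: for older infants, nothing ties the last session to a defined point in the stay.

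**Working it through.** **1. The plan's own figure.** Inputs from Sample size: difference 1.5, SD 3, power 0.9, total 258 (86 per arm if equal). Assumed, because not stated: two-sided 5%, pairwise, unadjusted.

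- n per arm = 2 × (1.960 + 1.282)² × 3² / 1.5² = 84.1, so 85 per arm and 255 in all, against 258 stated.
- At 86 per arm, SE = 3 × √(2/86) = 0.457, and power = Φ(1.5/0.457 − 1.960) = 0.906 (0.903 by the noncentral t).

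The figure reproduces, with no visible allowance for infants who contribute too little data.

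**2. What is fixed and what is open.**

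| Item | 32 weeks or less | Older |
|---|---|---|
| Number of sessions | minimum 3 | minimum 3 |
| Named time points | four | none |
| Named pre-discharge session | yes | no |
| Rule for which nearby procedure is filmed | none | none |
| Person arranging it knows the arm | yes | yes |

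The minimum number of sessions equals the three points that Statistical analysis asks for, so an infant who gives only the minimum has no margin.

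**3. Sensitivity: choice of occasion.** Suppose that in one arm the easier-looking of two eligible procedures is filmed for a share f of sessions, and that the prediction correlates r with the PIPP. The smaller of two standard normal values lies 0.564 below the mean on average, so

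shift = f × 0.564 × 3√(1 − ICC) × r.

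The inputs f, r and ICC are all assumptions.

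- Low end (f 0.25, r 0.2, ICC 0.7): 0.25 × 0.564 × 1.643 × 0.2 = 0.05 points.
- Middle (f 0.5, r 0.3, ICC 0.5): 0.5 × 0.564 × 2.121 × 0.3 = 0.18 points.
- High end (f 1, r 0.5, ICC 0.3): 1 × 0.564 × 2.510 × 0.5 = 0.71 points.

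With a bias b in the arm difference and no true effect, type I error = Φ(b/0.457 − 1.960) + Φ(−b/0.457 − 1.960). This gives 0.055 for b = 0.1, 0.085 for b = 0.25 and 0.19 for b = 0.5.

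**4. Sensitivity: infants below three sessions.** If such infants were left out of the analysis, and if the loss were equal in all arms:

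| Assumed loss | Infants per arm | Power for 1.5 points |
|---|---|---|
| 10% | 77.4 | 0.875 |
| 20% | 68.8 | 0.835 |
| 30% | 60.2 | 0.783 |

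**5. Sensitivity: a missing final session.** For one infant's straight line with equally spaced sessions, the variance of the fitted value at the intended end point is 1/n plus (end point − mean time)² / sum of squares of time, in units of the residual variance.

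- Four sessions, all obtained: 1/4 + 1.5²/5 = 0.70.
- Last one missing, extrapolated one step: 1/3 + 2²/2 = 2.33, which is 3.3 times larger.

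If time zero is instead the last session obtained, the variance problem eases but the comparison is made earlier in the stay.

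**6. How far a forecast stay matters.** If the last session is aimed at a fraction c of a single forecast, and the log forecast error has SD s, the chance of leaving first is Φ(ln c / s). For s from 0.2 to 0.4 this is 30% to 40% at c = 0.90, but 8% to 24% at c = 0.75. The result is driven by c and s, and the document gives neither.

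**The case against.** The strongest replies, and what stands of each:

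- **The nurse's freedom is limited.** Procedures are clinically ordered (Ethical considerations), timing is coordinated with staff, and younger infants have four named points. A minimum of three also fits a schedule in which some points coincide or are missed. This stands. A reader might infer that the nurse decides at will how many and which procedures count, and the text does not support that. What remains is the lack of a rule near each point, and of any points for older infants.
- **Choosing on the infant's state is hard.** The infant is in KMC at least 15 minutes before the procedure, or set up in the incubator or cot half an hour before, and parents are called ahead. Behavioural state is also itself scored in the PIPP. This weakens the calm-infant mechanism and favours the lower part of the range in step 3. It does not touch selection through the mother's availability or the timing of sessions.
- **This is a condensed article.** A filming manual may hold the rule. That is possible. But the article does state the number, the spacing and the person responsible, and states them loosely. If a rule exists, the remedy is to state it.
- **The model accepts unequal spacing.** It does, and that is harmless when timing is unrelated to arm and to expected pain. Here nothing secures that.
- **Lost last sessions are conjecture.** A reader might infer that final sessions will be lost in a third or so of older infants. The document reports no such loss, and wording that allows estimation also allows re-estimation. The loss of power in step 4 further depends on excluding infants with fewer than three points, which is an analysis choice rather than a result of the scheduling.

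**Conclusion.** The point holds as a design weakness: primary-outcome occasions are sampled after randomisation, with the arm known, under a minimum number and loose timing. Neither blinded coding nor tolerance of unequal spacing cures this. It applies to both age groups and is more open for older infants.

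The size cannot be derived from the document. The 0.05 to 0.71 point shift, the type I error of 0.085 at a 0.25-point bias, and the power of 0.875 to 0.783 at 10% to 30% loss are sensitivity figures resting on assumed shares, correlations, ICCs, loss rates and a two-sided 5% level. They show that modest selection could matter, not that it will, and the document gives no direction. The change is worth making because it costs little. The trial is not invalid without it. Confidence is medium.

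**What to change.** 1. Keep the existing time points for infants of 32 weeks or less. For older infants, name the target sessions, including one near discharge. Set and update the target dates by a rule that does not depend on arm; the existing randomisation website could issue them.
2. In all three arms, film the first routine heel lance or venipuncture on or after each target date that the mother can attend. Parents are already called in every condition, so the same requirement can apply to sucrose alone.
3. Log each eligible procedure passed over, with the reason, including the mother's absence. Staff documentation of all painful procedures is already monitored, so much of the denominator exists.
4. Report the number and timing of sessions by arm.
5. Analyse every filmed session in the mixed model, and drop the condition of three points per infant. This also fits the stated intention-to-treat principle.

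Purely early, fixed offsets for older infants would lose fewer sessions but would give up the late-stay data that hypothesis ii needs, so a near-discharge target is preferable.

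Cost: some wording, a date field, a short log and less scheduling flexibility. Clinical care is unchanged. One limit remains: filming only when the mother can attend leaves procedures done under the swaddling fallback unobserved. The rule makes that restriction the same in each arm, and the log makes it visible.

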## Methods

### Trial design

TRAKC is a single-blinded, randomized, parallel group design (Figure 1). The coders assessing the data will be blind to group assignment; however, the person completing the blood sampling will not be blind as it is impossible to prevent them from knowing participant KMC condition (i.e., skin-to-skin or incubator care).

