### Intervention conditions

#### *KMC condition*

If the infant is randomized to the KMC condition, the research nurse will begin by recording a one-minute sample of the infant in the incubator. The research nurse will then place the mother and infant into the KMC condition, where the diaper-clad infant is help upright, at an angle of approximately 60°, between the mothers breasts, providing maximal skin-to-skin contact between mother and baby. The infant will remain in KMC for at least 15 minutes prior to the painful procedure. Two minutes prior to the procedure the infant will receive ¼ of the recommended (based on NICU protocol) volume of sterile water by syringe onto the tongue. The remainder of the total recommended dose will be given as needed in small increments during the procedure.

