#### *Sucrose condition*

If the assigned condition is sucrose alone, half an hour before the procedure the nurse will place the infant in the supine position in an incubator or infant cot and set up the monitoring equipment. All monitoring will take place while the infant is in the incubator or cot. Two minutes prior to the procedure, the baby will receive ¼ of the recommended volume (based on NICU protocol) of 24% oral sucrose solution by syringe onto the tongue. The remainder of the total recommended dose may be given as needed in small increments during the procedure.

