### Outcomes

#### *Premature Infant Pain Profile (PIPP)*

The primary outcome in this trial will be infant pain intensity measured by the Premature Infant Pain Profile (PIPP) [72,88]. The PIPP uses seven indicators to calculate a composite pain measure: three behavioral indicators (facial actions of brow bulge, eye squeeze, and nasolabial furrow), 2 physiological indicators (heart rate and oxygen saturation), and 2 contextual indicators (gestational age and behavioral state) [72]. The contextual factors included in the PIPP are particularly important for this study as infants are being followed over time and therefore age changes will be accounted for. In addition, KMC is known to promote quiet sleep state, and this will be accounted for when considering behavioral state as an indicator in the PIPP scoring. The PIPP was developed 13 years ago and has steadily accumulated evidence of reliability and validity [72,88]. It had been used in over 40 studies to date [88].

This study will utilize a Somte (Compumedics, Melbourne, Australia) system that samples at a rate of 256 Hz to measure physiological data. Heart rate and oxygen saturation are recorded to the Somte system using a transcutaneous probe, and Electrocardiogram (ECG) is recorded from 3 leads. Epochs will be noted with an event timer in the Somte system. Close up video recordings of the infants face will be made using a Sony DCR-SR82 HDD digital video camera in the first baseline in the incubator (Baseline 1), one minute prior to start of procedure (Baseline 2), and during and after the procedure. The neurobehavioral state component of the PIPP score is determined according to Prechtl’s categories of quiet sleep, quiet awake, active sleep, or active awake [89], during the baseline [90]. Gestational age will be taken from the infant chart, and will be based on ultrasound at 16 weeks.

All data will be analyzed in the research laboratory outside the NICU. Physiologic data will be analyzed using Compumedics E-series Profusion PSG II software. Faces will be coded second-to-second on a stop frame system by trained coders naïve to the purpose of the study. Coders will be trained up to 90% agreement on video recordings from previous studies. Every three months, coders will recode randomly selected sessions (one from their earlier coding and one from each of the other coders) in order to determine both inter and intra-rater reliability.

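### The filming angle meant to keep coders blind imitates a prone infant in an incubator, but sucrose-alone infants lie supine, so the footage may separate both KMC arms from sucrose alone

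*Protocol article*

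**What the plan says.** All statements are in the protocol article.

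- **Trial design** bases the single-blind description on the outcome coders: "The coders assessing the data will be blind to group assignment". The person taking the blood sample is acknowledged not to be blind.
- **Procedures** gives the means. The research nurse keeps the camera on the face "at an angle that makes the infant appear prone in an incubator in order to keep coders" naïve. No arm is exempted from this instruction.
- **KMC condition** describes the real posture in that arm: "the diaper-clad infant is help upright, at an angle of approximately 60°, between the mothers breasts". Under **Combined KMC and sucrose condition**, "the infant will be placed in KMC as described for the KMC alone condition".
- **Sucrose condition** describes the comparator: "half an hour before the procedure the nurse will place the infant in the supine position in an incubator or infant cot". It adds: "All monitoring will take place while the infant is in the incubator or cot".
- **Premature Infant Pain Profile (PIPP)** describes what is filmed, "Close up video recordings of the infants face will be made", and says that the facial coders do not know what the study is for.

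**The concern.** Masking by camera angle works only if the disguised arms end up looking like the arm they are compared with. Here the disguise makes an infant held upright on the mother's chest look like one lying prone in an incubator, while the comparator infant is supine. If both instructions are followed as written, the footage may fall into two visual classes: apparently prone (KMC alone or combination) and supine (sucrose alone).

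That split coincides with the two contrasts against sucrose alone in the first hypothesis (1.5 points for KMC alone, 2 points for the combination). If coders came to associate one class with a treatment and an expectation, the subjective part of the primary outcome could shift in the direction hypothesised. The quarterly reliability checks would not reveal this, because agreement statistics do not detect a bias that all coders share.

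**Working it through.** **Step 1. Compare actual and filmed position by arm.**

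| Arm | Actual position | Position the camera angle is meant to suggest |
|---|---|---|
| KMC alone | Upright, about 60°, on the mother's chest | Prone, incubator |
| KMC plus sucrose | Same as KMC alone | Prone, incubator |
| Sucrose alone | Supine, incubator or cot, throughout monitoring | Prone, incubator (no arm exempted), but no means is given of making a supine infant look prone |

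The two KMC arms share one appearance, so this cue does not separate them. The sucrose-alone row is the one that does not fit.

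**Step 2. Identify which parts of the outcome are exposed.** The PIPP has seven indicators:

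- Three facial actions (brow bulge, eye squeeze, nasolabial furrow) are coded from the video and are exposed.
- Behavioural state is scored during the baseline. The article does not say that it is scored from the video, or which baseline is used, so it is possibly exposed.
- Heart rate and oxygen saturation are recorded by the Somte system, and gestational age comes from the chart. These three do not depend on face coding.

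The firm count is therefore three of seven, with a fourth possible.

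**Step 3. Reproduce the plan's sample size, as background for scale.** Inputs from Sample size: difference 1.5, SD 3, power 0.9, total 258. Two-sided alpha 0.05 and equal allocation are my assumptions, since the article states neither.

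- Normal approximation: n per arm = 2 × (1.960 + 1.282)² × 3² / 1.5² ≈ 84.1, rounded up to 85, or 255 in total.
- t-test version: 85.03, rounded up to 86, and 3 × 86 = 258. Power at 86 per arm is 0.903 (t) or 0.906 (normal).

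The figure of 258 is reproduced and is not in dispute.

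**Step 4. Illustrate what a coding shift would do.** The document gives no estimate of such a shift, so the values of b below are assumptions. With 86 per arm, the standard error of a difference in means is 3 × √(2/86) = 0.457. With no true difference and a shift of b points, the chance of a significant result in the direction of the shift is 1 − Φ(1.96 − b/0.457).

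| Assumed shift b (points) | b / 1.5 | Chance of a significant result in that direction (nominal 2.5%) |
|---|---|---|
| 0.25 | 17% | about 8% |
| 0.50 | 33% | about 19% |
| 0.75 | 50% | about 37% |
| 1.00 | 67% | about 59% |

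This is a simple two-group comparison at one time point, not the planned growth-curve model. It shows only that a shift well below the target difference would matter. It does not show that one will occur.

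**The case against.** The case on the other side has real weight.

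- **Close-up framing.** The recordings show the face, so body and surface may be largely out of shot. This reduces the cue. But Procedures itself treats position as visible enough to need a special angle, and no cropping or rotation is described, so face orientation and background remain possible cues.
- **Coders naïve to the purpose.** A coder who notices two postures but does not know what is being tested has no evident reason to score them differently. This is the strongest mitigating point and it stands as a reduction of risk. It is still less than the blindness to group that Trial design claims, and coders who see many sessions may notice a consistent pattern.
- **Structured coding.** Second-by-second stop-frame scoring, training to 90% agreement and three-monthly checks limit the room for drift. They do not detect drift common to all coders.
- **Coded syringes.** Identically packaged solutions help to mask KMC alone from the combination. They do nothing for KMC against sucrose alone.
- **Condensed reporting.** The filming instruction cites an earlier study, and the full protocol may hold more detail. That would excuse an omission. Here, however, the article states both the masking device and a comparator position that does not match it.

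A reader might also infer that KMC recordings betray themselves by a change of scene between the first baseline, in the incubator, and the second. The document does not support that: hiding the move is the purpose of the angle, and nothing says that the change would show in a facial close-up.

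**Conclusion.** The inconsistency stands. The masking described does not, as written, make the KMC arms look like the sucrose-alone arm, and the cue may be visible in the contrasts that matter most. The three coded facial indicators are open to bias, and behavioural state possibly so.

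Three stronger conclusions are tempting and are not supported:

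- **That coders can tell the arm, so blinding of the primary outcome fails.** Detection is an inference, and the close-up framing and the coders' naivety both weigh against it.
- **That the whole PIPP score lacks protection.** Heart rate, oxygen saturation and gestational age do not depend on face coding.
- **That the bias has a known size.** The shifts tabulated above are assumed, and nothing in the document allows one to be estimated.

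KMC alone against the combination is unaffected by this cue. The point merits correction because it touches the credibility of the primary outcome and can be remedied in the laboratory.

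**What to change.** Reconcile Trial design, Procedures and Sucrose condition so that they state how coded footage is given the same apparent position in all three arms. This can be done on the recordings alone, and no change to how infants are positioned is proposed. One workable form:

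1. Before coding, crop every clip to the face and rotate it to a common orientation, so that surface and posture are not visible. Apply the same processing in all arms.
2. Preserve the matching of each phase to the Somte timer, so that facial and physiological data remain aligned.
3. Ask coders to guess the arm once, after all coding is finished, and report the result by arm. Asking during the study, for instance at the quarterly re-coding, would alert coders to the existence of arms and weaken the naivety on which the plan relies.

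The cost is modest video-handling time in the laboratory, for at least three recorded sessions per infant, plus one short form at the end. The processing can also be applied to recordings already made, provided that they have not yet been coded.
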